Participants randomized to control will be told that they are eligible to form microclinic groups following the conclusion of the study. They will be counseled on the importance of social support in their HIV care and will be clearly advised that assignment to the control group should not prevent them from discussing their HIV care with those close to them. As is true for all participants who are recruited for the study, they will be advised to return to the clinic. Beyond the counseling to return to clinical HIV care provided by study staff, standard of care for patients who have missed a clinic visit is to receive a follow-up visit from clinic staff to facilitate return to care. Study staff will collaborate with clinic staff to ensure that all study participants receive a visit from study staff and clinic staff to encourage return to care.

Orientation meetings will be conducted on a bi-monthly (every other month) basis with all newly formed microclinic groups. This meeting will include the following:

- The microclinic intervention will be explained to all prospective group members and a brief orientation to the curriculum will be provided.
- Study enrollment of social network members who were not originally enrolled through eligibility determination at the clinic. These ‘social network members’ will be consented for study participation (See Appendix I, Consent document for Microclinic Group Members), but will not be included in primary study analysis. Data from these participants will only be used for purposes of understanding the characteristics of those who were selected for microclinic participation and how their characteristics impact outcomes among index participants. For ‘social network’ participants, study participation will involve survey administration and data collection on participant HIV and clinic status in order to understand microclinic group composition. Study enrollment is voluntary and refusal will not prevent social network group members from participating in the microclinic group meetings. Aside from reasons for refusal, no data will be collected for social network participants refusing study enrollment.
- All group members will undergo individual confidential HIV testing (group members who are known to be HIV-infected will attend a counseling session but will not be tested).

[figure not shown]

**Figure 1.** Participant flow diagram

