The microclinic intervention includes participation by members of the index patient’s social network. This may include other index patients, or community members who are HIV-infected, HIV-uninfected or of unknown HIV status. These non-index microclinic members, referred to as ‘social network’ participants, will be invited to join the study in addition to participation in a microclinic group. Microclinic participant is not contingent on study participation, however data will only be collected for microclinic group members who also consent to study participation.(Appendix I) For social network participants, study participation involves completion of a baseline survey to collect information on sociodemographic characteristics, HIV-related stigma, previous HIV testing, HIV status, and enrollment and engagement in HIV care (if HIV-infected).(Appendix D) For each microclinic group, a Microclinic Group Member Information form will also be completed to describe the nature of the realtionships between group members.(Appendix E) Only group members who consented to study participation will be included. At the time of group enrollment, all prospective social network study participants will be invited to enroll in the study. Following study enrollment, these surveys to collect information on sociodemographic characteristics and HIV-related stigma will be administered by trained study staff. Data on previous HIV testing, HIV status and enrollment and engagement in HIV care will be collected by a trained Voluntary Counseling and Testing (VCT) counselor as part of a baseline HIV counseling and testing session. Refusal to participate in the study will not preclude social network group members from participating in the microclinic group, but no study data will be collected on these participants.

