### Adverse Events

All study participants in both study arms will be asked to complete an end-of-study survey. This survey will include an open-ended questions about any adverse events experienced over the course of thes study (Appendix G). Risk of any adverse event will be compared between index participants in the two study arms, and risk of adverse events will be described among ‘social network’ members who participated in the microclinic intervention. All participants reporting an adverse event will be offered counseling by a trained VCT counselor and/or a staff member at the participant’s preferred health facility.

In addition to self-reported adverse events, clinic staff will also review participant medical records on a monthly basis. Appendix N outlines study procedures for reporting adverse clinical events to the KEMRI Ethical Review Committee.

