| **SECTION B. MISSED VISITS**  ***Only for patients who miss a visit by 30-days and then come back to the same clinic. All other types of care gap will be addressed by LTFU form.*** | | | | | | | | |
| B1. During the past 12 months, did you receive more than 2-weeks supply of HIV medications from any source other than your regular clinic? | | | | | | | | |
|  Yes | B1a. What sources did you receive medication from? | | | B1b. What months did you receive medication from each of these sources? | | | | B1c. What type of medication? *(check all that apply)* |
|  Another clinic, name: | | |  | | | |  CTX   ARVs |
|  Family/friends | | |  | | | |  CTX   ARVs |
|  Other, specify: | | |  | | | |  CTX   ARVs |
| ** For any additional clinics patient visited, collect visit history from transfer clinics using VISIT HISTORY FORM** | | | | | | | |
|  No | ** go to SECTION C** | | | | | | | |
| **SECTION C. DISCLOSURE** | | | | | | | | |
| C1. Not counting healthcare workers, have you disclosed your HIV status to anyone? | | | | | | | | |
|  Yes | | C1a. Not counting healthcare workers, how many people have you disclosed your status to? | | | | C1b. Which groups of people have you disclosed to?  (check all that apply) | | |
| Number of people |  Too many to count   Refuse to answer | | | 1  Sexual partner  2  Other family  3  Friends  4  Coworkers  5  Members of a group (e.g. support group, church, etc)  6  Other, specify: | | |
|  No | | ** skip to SECTION D** | | | | | | |

| **SECTION D. HIV-RELATED STIGMA** | | | | | |
| --- | --- | --- | --- | --- | --- |
| **How do you feel about being HIV positive?** | **Strongly disagree** | **Disagree** | **Neutral** | **Agree** | **Strongly Agree** |
| D1. Having HIV makes me feel like I’m a bad person |  |  |  |  |  |
| D2. I feel I’m not as good as others because I have HIV |  |  |  |  |  |
| D3. I feel ashamed of having HIV |  |  |  |  |  |
| D4. I think less of myself because I have HIV |  |  |  |  |  |
| D5. Having HIV makes me feel unclean |  |  |  |  |  |
| D6. Having HIV is disgusting to me |  |  |  |  |  |
| **How likely is it that people will treat you in the following ways in the future because of your HIV status?** | **Very unlikely** | **Unlikely** | **Neither unlikely nor likely** | **Likely** | **Very likely** |
| D7. Family members will avoid me |  |  |  |  |  |
| D8. Family members will look down on me |  |  |  |  |  |

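### The protocol promises to describe adverse events among social network members, but its data-use clause, its definition of their participation and its single closing form do not support that description

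*Protocol*

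**What the plan says.** Four parts of the protocol bear on this.

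- **Adverse Events.** "All study participants in both study arms will be asked to complete an end-of-study survey", and from it "risk of adverse events will be described among ‘social network’ members who participated in the microclinic intervention". Clinic staff also review participants' medical records monthly.
- **Subject Recruitment and Enrollment.** On enrolled network members: "Data from these participants will only be used for purposes of understanding the characteristics of those who were selected for microclinic participation", and how those characteristics affect outcomes in index participants. Their participation is a survey and "data collection on participant HIV and clinic status in order to understand microclinic group composition".
- **Study Design Overview.** "For social network participants, study participation involves completion of a baseline survey", with HIV testing history and care status taken at a baseline counseling session. Members may be "community members who are HIV-infected, HIV-uninfected or of unknown HIV status".
- **Measurements, and the end-of-study form (Appendix G).** Measurements promises an open-ended question on adverse experiences for everyone. For the intervention arm it also promises a checklist and an open-ended question on harms from group disclosure. The printed form runs from Section A to Section G. Section D opens with "How do you feel about being HIV positive" and has no branch for other respondents.

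**The concern.** One section commits to a safety description. Two others, which define what network members contribute and what their data are for, leave no place for it. The instrument that would supply the data was written for HIV-infected patients.

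The exposure is real. Members are tested for HIV at orientation and offered the same group testing and disclosure as index participants. Under Potential risks and discomforts, the protocol names breach of confidentiality and reputational harm from unintended disclosure as the main risk. Medical record review cannot reach members who have no clinic record. Counseling is offered to those who report an adverse event, so a member who is not surveyed has no stated route to it.

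If the intervention is rolled out as the protocol foresees, a harms statement resting on index participants, or on whichever members the form happened to suit, would be an incomplete account of its risk.

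**Working it through.** **1. The texts side by side**

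| Question | Adverse Events | Recruitment / Study Design Overview |
|---|---|---|
| Are members' harms to be reported? | Yes, descriptively | Not among the permitted uses; the clause says *only* |
| Is there a closing contact? | Yes, if all study participants includes enrolled members | Only baseline data collection is named |
| Which members? | Those who took part in the intervention | Of any HIV status |

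Other sections suggest that the closing operation was built around index patients. The List of Appendices has separate baseline forms for index participants and group members but one end-of-study form. Payments to subjects ties survey compensation, at baseline and closure, to participants who missed clinic visits.

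**2. Does Appendix G fit a member who is uninfected or of unknown status?**

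- Section A is completed from clinic data, so it is not put to the respondent.
- Section B is limited to patients who missed a visit and came back to the same clinic, so others bypass it.
- Section C (disclosure of own status) has a near-identical item on the members' baseline form.
- Section D (stigma) presumes an HIV diagnosis. It does not fit.
- Sections E and F include support with HIV clinic visits and HIV medication. Those items do not fit.
- Section G (group participation and group testing) fits.

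**3. Does Appendix G measure harm in anyone?** The printed form has no open-ended adverse-event question and no disclosure-harm checklist. The nearest item is a tick-box in Section G for having been pressured by the group into group testing. The stigma items ask how others have treated the respondent, but only in relation to an HIV diagnosis, and they do not ask about attribution to the study.

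**4. Size of the exposed group.** The protocol gives no figure to reproduce. Inputs: up to 180 index participants per arm and an average of 2 per group (Sampling); 5-10 people per group (Abstract), or five to ten recruited network members (Subject Recruitment and Enrollment); 72 of 93 (77%) participating in the pilot (Sampling).

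- Groups = 180 / 2 = 90.
- If 5-10 is total size: 90 × (5 − 2) = 270 to 90 × (10 − 2) = 720 members. Ratio to 180: 1.5 to 4.
- If 5-10 are recruited per group: 90 × 5 = 450 to 90 × 10 = 900 members. Ratio: 2.5 to 5.
- At 77% uptake: 180 × 0.77 = 138.6 index participants in 69.3 groups, giving about 208 to 554 or 347 to 693 members. The ratio per index participant in a group is unchanged. Against all 180 assigned it is 208 / 180 = 1.2 to 693 / 180 = 3.9.

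Network members outnumber intervention index participants on every one of these readings.

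**The case against.** The strongest reply is that a collection route exists. The Adverse Events paragraph distinguishes index participants from network members, so its reference to all study participants plausibly covers both. Cost to subjects mentions surveys before and after the intervention without exempting members. The Study Design Overview says what participation involves, not that it stops there. The word *only* in the recruitment section follows a sentence keeping members out of the primary analysis and may be loose drafting aimed at efficacy. All of this stands as far as it goes.

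It also disposes of several stronger readings that a reader might infer:

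- *That the description would be empty, or that no member has a usable closing form.* The route just described, and Sections C and G of the form, do not support that.
- *That the whole form presumes an HIV patient.* Sections A and B are not put to non-patients.
- *That the exposed group could reach 1,170.* That is 90 × (15 − 2), using the general group size of 5-15 in the Introduction rather than this trial's 5-10.
- *That collecting nothing from attendees who decline enrolment is a defect.* It is proper and openly stated. It matters only for the denominator.

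The reply does not remove the data-use clause, which on its wording excludes the planned description even if the survey is given. Nor does it repair Section D, or supply the adverse-event items missing from the printed form. The group-member consent is not in the review copy. It may mention a closing survey, but it could not settle a conflict within the protocol itself.

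**Conclusion.** The point holds as an internal inconsistency with a practical consequence: the safety description promised for network members is not validly deliverable as the protocol is written. It concerns about 1.5 to 5 members per index participant in a group. The ratio rests on the protocol's average of 2 index participants per group and on the reading of 5-10. The headcount also depends on uptake and on how many members agree to enrol. The finding on Appendix G rests on the form as it appears in the review copy.

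The effect is confined to harms reporting. Network members are outside the primary analysis, and no randomised comparison, outcome or power statement changes. The missing adverse-event items reach further than network members, because the planned comparison of adverse-event risk between index participants in the two arms relies on the same form.

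**What to change.** 1. In Subject Recruitment and Enrollment, add safety reporting to the permitted uses of enrolled members' data. In the Study Design Overview, name the end-of-study adverse-event survey as part of their participation. Both sections then agree with Adverse Events.
2. In Appendix G, add the open-ended adverse-event question and the disclosure-harm items already promised in Measurements and Adverse Events, as a stand-alone section for all participants. Add a skip rule so that members not known to be HIV-infected bypass the items on being HIV positive and on HIV care.
3. Report the network-member risk with its denominators: members enrolled, members surveyed, and attendees who declined enrolment. Reasons for refusal are already recorded, so the last can be counted.

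The cost is amendment wording, one form section with a skip rule, and a few minutes per enrolled member at closure, a contact that Adverse Events can already be read to promise. The group-member consent should be checked to confirm that it covers the closing survey and this use of the data.

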## Data Analysis

Primary analyses will be conducted using only the index study participants (i.e. participants who are HIV-infected and who missed a clinic visit by >3 days to become eligible for study participation).

Hypothesis 1

We will compare the indicence of 90-day absence from clinical HIV care between study arms using a Cox proportional hazards model. Additionally, we will depict the cumulative incidence of 90-day absence using the Cumulative Incidence Function, with death as a competing event.[24](#_ENREF_24) Primary analysis will be unadjusted, with standard errors adjusted for clustering of participants who are in the same microclinic group. Validity of the proportional hazards assumption will be assessed graphically and through formal testing using Schoenfeld residuals.

Hypothesis 2

‘Time in care’ will be calculated for each participant by subtracting the total days ‘out of care’ from the total length of follow-up and divided by the total length of follow-up. This will constitute a proportion depicting the proportion of time a given participant has spent adhering to his or her clinic appointment schedule. The number of days ‘out of care’ will be calculated by summing the total number of days between missed appointments and next clinic visits for each participant over the course of follow-up. Analysis will be conducted using linear regression to compare the mean proportion of ‘time in care’ between study arms. Standard errors will be adjusted for clustering, as in Hypothesis 1. Bootstrapping with cluster re-sampling will be conducted to address potential non-normality of residuals. Primary analysis will be conducted using unweighted time in care proportions for all participants, with sensitivity analysis conducted where each participant is weighted according to the length of follow-up.

Hypothesis 3

Because all eligible study participants will have recently missed an appointment, we are interested in the rate of reconnection to care. Reconection to care will be defined as return to any HIV clinic and receiving a refill of that patient’s ART or co-trimoxazole prophylaxis. We will depict time to reconnection to care by study arm using the Cumulative Incidence function, with death as a competing event.[24](#_ENREF_24) We will formally test the differece in the rate of reconnection to care using a Cox proportional hazards model. Standard errors will be adjusted for clustering, as in Hypothesis 1. Validity of the proportional hazards assumption will be assessed graphically and through formal testing using Schoenfeld residuals.

Hypothesis 4

The proportion of paritipcants alive and retained in care at the end of 12 months of follow-up will be compared between study arms using simple chi-squared analysis. Retention is defined as being alive and not missing a clinic appointment by 90 days or more as of study closure at 12 months post- study enrollment.

Hypothesis 5

The proportion of participants who are alive and virally suppressed at the end of the study will be compared between study arms using chi-squared testing. Viral load testing conducted within 180 days of the 12-month timepoint post study enrollment will be used for analysis. As above, viral loads utilized for analysis will be collected during routine patient care. Primary analysis will be conducted on an intention to treat basis, with missing values assumed to be virologically non-suppressed. Sensitivity analysis will be conducted using completer analysis, where only participants with measured viral loads will be included. In this sensitivity analysis, participants who died or who disengaged from care will be included as virologically non-suppressed.

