## Sampling

*Sample Size Calculation*

Sample size calculations were generated based on preliminary data from the Mfangano Island Healthy Network Impact Study (MIHNIS). The MIHNIS study was a quasi-experimental study with the intervention delivered to one community and neighboring communities acting as control groups. Additionally, the proposed clinic sites were visited in September 2014 to assess rates of missed clinic appointments to help ground sample size estimates in the realities of each individual clinic.

During the six months prior to delivery of the intervention in the MIHNIS study, 268 of 410 (65%) patients on ART at the Sena Health Center missed a clinic visit by >3 days. Of these, 238 (89%) joined the study. Among the control group in the MIHNIS study, 36 of 145 (25%) participants who missed a clinic visit by more than 3 days during the 6 months enrollment period had a 90-day clinic absence within the following 12 months. Among patients eligible for the intervention and who missed a clinic visit by >3 days during the enrollment period, 72 of 93 (77%) actually participated in the microclinic intervention. In the MIHNIS study participants in the intervention community had a more than 50% lower rate of 90-day disengagement than those in the control community, regardless of intervention uptake.

Thus, we assume an event rate of 0.25 in the control group and 0.125 in the intervention group. Setting alpha to 0.05 and beta to 0.2 and assuming an average of 2 participants per group with a coefficient of variation of 0.25, we will need 156 index participants per study arm. This sample size accounts for non-independence of outcomes introduced by the clustered nature of the intervention. Allowing for 10% participant attrition, we would need to sample 175 participants per study arm. The MIHNIS study ascertained outcomes for 98.6% of study participants, thus the allowance for 10% attrition in the proposed study is conservative.

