## Subject Recruitment and Enrollment (Figure 1)

Following sampling at the clinic, study staff will coordinate with clinic staff to obtain locator information and attempt to locate the potential participant in the community. Once identified, study staff will work with clinic staff to locate the patient to both encourage return to the clinic and invite them to join the study.

After explaining the study and answering all questions, eligible participants will be invited to enroll. Participants will be read the study consent form and will be asked to sign. If patient is illiterate, the participant will be asked to identify a witness who can co-sign the consent and help ensure that the participant fully understands all risks and benefits of the study.Following enrollment, participants will be randomized to either the intervention or control arm. Randomization will be conducted using sealed envelopes stratified by clinic site. Staff will open the next sequentially numbered envelope and will notify participants of their randomization allocation.

Participants randomized to intervention will be invited to form ‘microclinic’ groups. Microclinic formation involves recruitment of five to ten members of their social networks who they commonly rely upon for support (ie family members, friends, neighbors, co-workers, church members, etc). Study staff will assist in group recruitment and formation according to the preferences of the participant (i.e. participant will be asked whether they want to approach potential group members themselves or whether they want study staff to confidentially approach potential group members to invite them to participate). This process mirrors that used in our previous Mfangano Island Healthy Network Impact study (MIHNIS).

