A full clinic visit history will be obtained for all study participants on HIV care and treatment at any of the included study sites. Visit history data will be obtained from the FACES-MOH “Blue Cards”. For patients who made an official tranfer to another facilities within Nyanza Province, study staff will visit that facility to confirm the transfer and obtain a complete clinic visit history following the transfer. In addition to data on clinic visit attendance, patient enrollment date, ART initiation date, ART regimen, CD4 measurements, viral load measurements, pharmacy pick up, vital status and locator information will also be collected. All participants lost to follow-up from clinical care during the course of the study will be traced to ascertain vital and clinical status (i.e. disengagement from any clinical care, transfer to another facility, death while ‘in care’ or death after disengaging from care). For patients who made an unofficial transfer to another health facility in Nyanza Province, study staff will visit that facility to obtain visit history as was described for the official transfers. For patients who are disengaged from clinical care at the time of tracing, barriers to return to care will be identified and participants will be counseled to return to care. Clinic staff will be informed of any additional information gained in the field regarding the vital or clinical status of patients who were lost to follow up from clinical care.

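### Clinic stratifies the randomisation but is left out of the analyses, and H2 makes no use of prior attendance: the tests stay valid, but some precision is given up

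*Protocol*

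**What the plan says.** Protocol, section VIII.D (Subject Recruitment and Enrollment): "Randomization will be conducted using sealed envelopes stratified by clinic site". Staff open the next numbered envelope. No blocking or other restriction within clinic is mentioned.

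Section VIII.G (Data Analysis):
- **Hypothesis 1** (90-day absence) uses a Cox model: "Primary analysis will be unadjusted, with standard errors adjusted for clustering of participants who are in the same microclinic group".
- **Hypothesis 2** (time in care) compares arm means by linear regression. It takes over the clustering of standard errors from Hypothesis 1 and adds a cluster bootstrap. It names no clinic term and no covariate. Its one sensitivity analysis weights participants by length of follow-up.
- **Hypothesis 3** (reconnection to care) is a Cox model with the same clustering.
- **Hypotheses 4 and 5** (retention, viral suppression) are chi-squared comparisons.

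Section VIII.F (Study Design Overview): "A full clinic visit history will be obtained for all study participants on HIV care and treatment at any of the included study sites". The Measurements subsection also lists a complete visit history among the chart-review data.

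Section VIII.C (Sampling) sizes the trial on 90-day absence alone: "we assume an event rate of 0.25 in the control group and 0.125 in the intervention group", leading to "we will need 156 index participants per study arm".

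**The concern.** A factor is normally used to stratify randomisation because it is expected to predict outcome, and the analysis then respects it. Here the sponsor stratified on clinic, and the Hypothesis 1 wording leaves clinic out of the primary model. This is a stated choice, not a detail deferred to a later plan.

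Clinics plausibly differ. In Table 1 the share of adult patients on ART is 427/549 = 78% at Sena, 185/397 = 47% at Wakula, 66/153 = 43% at Ugina and 14/40 = 35% at Soklo. That does not prove that absence rates differ, but it makes a difference credible.

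For Hypothesis 2, the outcome is computed from visit history, so for most participants the same quantity can be computed before randomisation. A baseline measure of the outcome is usually the most useful covariate available, and here it costs no extra data collection. What is at stake is precision on both primary outcomes.

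**Working it through.** **1. The Protocol's own sample size.** The inputs are in Sampling: "Setting alpha to 0.05 and beta to 0.2 and assuming an average of 2 participants per group with a coefficient of variation of 0.25", with event rates 0.25 and 0.125. Two-sided alpha is assumed, since sidedness is not stated. The Hayes–Bennett formula for proportions gives

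clusters per arm = 1 + (1.960 + 0.842)² × [p0(1−p0)/m + p1(1−p1)/m + k²(p0² + p1²)] / (p0 − p1)²

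- Bracket: 0.09375 + 0.05469 + 0.00488 = 0.15332.
- Divided by 0.125² = 0.015625: 9.8125.
- Times 7.849: 77.02. Plus 1: 78.02 clusters.
- Times m = 2: 156.03 per arm, against the stated 156.
- Attrition: 156/0.9 = 173.3, so 174, against the stated 175.

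The stated power therefore reproduces without any covariate or stratum.

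**2. Hypothesis 1: what stratifying by clinic would add.** The Protocol gives no between-clinic variation, so this was simulated over an assumed range:
- 312 participants in 8 clinics, weighted by Table 1, with about 225 East residents removed from Sena to reach the Protocol's figure of about 1,500 (assumption).
- Marginal 12-month event rates held at 25% and 12.5%. With no clinic variation the hazard ratio is ln(0.875)/ln(0.75) = 0.464.
- Unstratified against clinic-stratified log-rank test (the Cox score test), 4,000 replicates per scenario. Microclinic clustering is ignored, so absolute power is slightly optimistic.

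| SD of clinic log hazard | Allocation within clinic | Power, unstratified | Power, stratified | Type I error, unstratified |
|---|---|---|---|---|
| 0 | blocks of 4 | 82.0% | 81.8% | 4.8% |
| 0.3 | blocks of 4 | 81.8% | 82.0% | 4.7% |
| 0.6 | blocks of 4 | 80.9% | 82.1% | 3.9% |
| 1.0 | blocks of 4 | 82.1% | 85.7% | 3.4% |
| 0 | no blocks | 81.8% | 80.6% | 4.9% |
| 0.3 | no blocks | 81.7% | 80.8% | 5.4% |
| 0.6 | no blocks | 82.2% | 82.8% | 5.1% |
| 1.0 | no blocks | 79.7% | 83.9% | 4.7% |

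The Monte Carlo standard error of a power near 82% is √(0.82 × 0.18/4000) = 0.6 points. Up to SD 0.6 the change runs from about −1 to +1 point. At SD 1.0 it is about 4 points. The unstratified test is conservative only under blocking, and noticeably so only when clinics differ a lot.

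**3. Hypothesis 2: what adjustment would add.** If prior and on-study time in care correlate at r, the residual variance is multiplied by 1 − r² and the standard error by √(1 − r²). The Protocol gives no r and no power for Hypothesis 2. For illustration, the effect is set to give 80% power unadjusted at 156 per arm.

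| r (assumed) | Variance factor | SE factor | Power |
|---|---|---|---|
| 0.2 | 0.96 | 0.980 | 81.6% |
| 0.3 | 0.91 | 0.954 | 83.6% |
| 0.5 | 0.75 | 0.866 | 89.9% |

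At the planned maximum of 2 × 180 = 360, r = 0.3 is worth 360/0.91 − 360 = 36 extra participants and r = 0.5 is worth 360/0.75 − 360 = 120. A clinic term alone, with assumed clinic ICC of 0.01, 0.05 or 0.10, gives 80.4%, 82.0% or 84.0% power.

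**The case against.** An unadjusted, pre-specified intention-to-treat comparison is valid, simple and hard to manipulate. The planned size does not depend on adjustment, and there is some margin: enrolment may go to 180 per arm, and the Protocol calls its 10% attrition allowance conservative because the earlier study ascertained 98.6% of outcomes. All of this stands.

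Three stronger readings are tempting, and the Protocol does not support them.

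- **That Hypothesis 1 misses its stated power.** The 156 per arm reproduces, and unstratified power in the simulation stays at about 80 to 82% throughout.
- **That the standard error is too large because clinic is ignored.** Conservatism needs balance forced within clinic, and no blocking is stated. Without it, type I error was 4.7 to 5.4%. In a Cox model, adjustment does not generally shrink the standard error of the log hazard ratio. Any gain comes from a within-clinic effect further from the null, or from removing conservatism.
- **That the Protocol rules out adjustment for Hypothesis 2.** The unadjusted sentence sits under Hypothesis 1. Hypothesis 2 imports only the clustering and names no covariate. An analysis plan that is not at hand could add one.

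The Hypothesis 2 gain also has limits. First-time initiators are eligible and have no prior history. Transfers-in may have none at the study sites, and the history collection described covers those sites and transfers out. Everyone is selected on a recent missed visit, which may narrow the spread of prior attendance and lower r.

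**Conclusion.** The point holds as a matter of efficiency and of mismatch between design and analysis. It is not an error in the stated power, and it does not threaten validity.

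The gain for Hypothesis 1 is small unless clinics differ strongly. Hypothesis 2 is the stronger half, because the covariate is the outcome's own earlier value and is largely in hand. Its 9 to 25% variance reduction rests entirely on the assumed r of 0.3 to 0.5 and applies only where prior history exists. The Hypothesis 1 figures rest on the assumed clinic SD, the clinic weights and the omission of microclinic clustering.

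**What to change.** Pre-specify the following before outcome data are seen:

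- **Hypotheses 1 and 3:** Cox models stratified by clinic, keeping the microclinic-clustered standard error. State a pooling rule for the smallest clinics, for example by island.
- **Hypothesis 2:** linear regression with clinic indicators and time in care over a fixed window before randomisation (up to 12 months). Add a no-prior-history indicator for new initiators and for transfers-in without records.
- **Hypotheses 4 and 5:** a clinic-stratified test in place of the simple chi-squared test.
- **All:** keep the unadjusted analyses as supportive, and state whether the envelopes are blocked within clinic.

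The cost is analysis wording, with no new data collection. There are two small downsides. The stratified Cox model estimates a within-clinic (conditional) hazard ratio, which differs from the marginal one and should be labelled as such. Very small clinics carry little information: of 312 participants, Soklo would supply about 312 × 40/1500 = 8 and Nyakweri about 312 × 49/1500 = 10. At an average event rate of 0.1875 that is one or two events each, hence the pooling rule.
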